### Process evaluation

To assess the feasibility of the ´Stay Active at Home´ programme, data from older adults, home care professionals, and other stakeholders (e.g. interventionists, managers) will be collected. A process evaluation plan is designed according to the guidelines of the MRC framework [62]. According to the guidelines key elements are: 1) the implementation of the intervention; 2) its mechanisms of impact; and 3) contextual factors that may affect its implementation and outcomes.

#### Implementation: What is implemented and how?

An intervention may have limited effects either because of weaknesses in its design or because it is not well implemented [62]. To be able to draw reliable conclusions about the effectiveness of the ‘Stay Active at Home’ programme, the implementation of the programme will be evaluated. More specifically, data on treatment fidelity (quality of implementation), dose (quantity of implementation), adaptations (alterations made) and reach (whether the intended audience comes into contact with the intervention) will be collected.

#### Mechanisms of impact: How does the delivered intervention produce change?

For an understanding of how potential effects occur, it is essential to get insight into how an intervention produces change [62]. The ‘Stay Active at Home’ programme aims to change the behaviour of home care professionals from doing things *for* the client towards doing things *with* them. Therefore, the programme intends to 1) increase knowledge; 2) improve self-efficacy and outcome expectations; 3) teach new skills; and 4) provide social support. The process evaluation will examine whether the ‘Stay Active at Home’ programme produces changes through these mechanisms.

#### Context: How does context affect implementation and outcomes?

The implementation and effectiveness of interventions may vary from one context to another due to external factors, which may act as a barrier or a facilitator [62]. Therefore, data from various stakeholders will be collected to get insights into their experiences with the ‘Stay Active at Home’ programme. More specifically, stakeholders will be asked which factors have hindered or facilitated the implementation of Reablement in practice. Insight into these factors is critical to understand the implementation and effectiveness of the ‘Stay Active at Home’ programme.

A mixed-methods design will be chosen for data collection, combining quantitative and qualitative data collection methods. More specifically semi-structured (group) interviews, telephone interviews, a project logbook, registration forms and checklists, client records, and self-report questionnaires will be used to measure the key components. An overview of all data that will be collected according to these three elements is provided in Table 3.

**Table 3 Tab3:** Overview of process evaluation data collection

Component and definition	Data source	Arm	Data collection method	Specific data^a^	Timing
Implementation					
*Fidelity* Quality of what is delivered	Professionals and other stakeholders (e.g. interventionists, managers)	IG	Semi-structured (group) interviews	– a.o. experienced benefits, burden, usefulness of ‘Stay Active at Home’; involvement with intervention	At the end of the implementation phase
	Older adults	IG, CG	Telephone interviews	– a.o. satisfaction with home care and awareness of behavioural change in professionals	6 months after baseline (with data for effect and economic evaluation)
	Researchers	IG	Project logbook	– Performance according to protocol	Continuously throughout the implementation phase
*Dose* Quantity of what is delivered	Professionals	IG	Registration forms and checklists	– Number of professionals: attending programme meetings; making practical assignments; reading weekly newsletters	Continuously throughout the implementation phase
	Older adults	IG	Client records	– a.o. hours of care; staff turn-over trained professionals; formulation and implementation of goal-setting and action planning	At the end of the implementation phase
*Adaptations* Alterations made to the intervention	Researchers	IG	Project logbook	– if applicable: changes in content, procedures, activities and processes	Continuously throughout the implementation phase
*Reach* Extent to which the target group was reached	Professionals	IG	Project logbook	– Number of professionals who will refuse, drop out or complet the programme and reasons for refusal and drop-out	Continuously throughout the implementation phase
	Older adults	IG	Project logbook	– Number of older adults who will refuse, drop out or complete the programme and reasons for refusal and drop-out	Continuously throughout the implementation phase
Mechanisms of impact					
Mechanisms that are expected to produce change	Professionals	IG, CG	Self-report questionnaire	– Knowledge test and self-efficacy and outcome expectation questionnaire inspired by the work of Resnick et al. [75–77] – Additional evaluation questions (which cover the different topics of the programme)	6 and 12 months after baseline
	Older adults	IG, CG	Self-report questionnaire	– Self-efficacy and outcome expectation questionnaire inspired by the work of Resnick et al. [78]	6 and 12 months after baseline (with data for effect and economic evaluation)
Contextual factors					
Factors that may influence the implementation/ outcomes of the intervention	Professionals and other stakeholders (e.g. interventionists, managers)	IG	Semi-structured (group) interviews	– a.o. facilitators and barriers in applying ‘Stay Active at Home’ in practice	At the end of the implementation phase
	Researchers	IG	Project logbook	– a.o. facilitators and barriers in applying ‘Stay Active at Home’	Continuously throughout the implementation phase

*IG* intervention group, *CG* control group

^a^Need to be further specified

### Sample size

The sample size calculation will be based on the primary outcome of this study, namely sedentary time as measured by the ActiGraph GT9X Link (ActiGraph Inc., Pensacola, FL, USA). The ‘Stay Active at Home’ programme is expected to create a 15% difference in sedentary time (minutes/ day) between the groups. Based on a mean of 535.9 min (*SD* = 145.7) [45] this is equivalent to an effect size of 0.55, which can be interpreted as a medium effect size according to Cohen [63]. To achieve a power of 80% with an alpha of 0.05 (using two-tailed tests) requires a minimum sample size of 54 clients per group *(N =* 108 in total). Considering an expected drop-out rate of 30% before post-test, a total sample size of 154 older adults is needed. Finally, to compensate for a) the inflation of sampling error arising from a clustering effect and b) a mild variation in sample size per nursing team, a correction will be applied, taking into account an intraclass correlation of 0.02 and a coefficient of variation of 0.50, resulting in a total sample size of 260 older adults (130 for each arm) [64].

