### Randomisation

For this study, ten nursing teams in five working areas (two teams per area) will be selected by the nursing team managers of MeanderGroep. To avoid contamination bias, managers will be asked to select two teams within each area that are not collaborating with each other. Furthermore, dementia teams will not be considered, as most of their clients potentially will not fulfil the inclusion criteria for older adults. The nursing teams will be pre-stratified with regard to their working area and randomised into either the intervention or control group within each working area. The clients and, if applicable, their DSWs will be allocated to the intervention or control group based on the allocation of the nursing team. The randomisation will be conducted by means of a computer-generated randomisation list. The researcher who will conduct the randomisation, will be blinded, will not be involved in this study and not familiar with the nursing teams. A flow diagram of the study design is shown in Fig. 1.

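### The stated 80% power makes no allowance for ten teams in five area pairs; with about 4 team-level degrees of freedom, a post-test comparison on the plan's inputs has roughly 58–67%

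*Protocol article*

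**What the plan says.** The Sample size section assumes that the programme "is expected to create a 15% difference in sedentary time (minutes/ day) between the groups". With a mean of 535.9 min and an SD of 145.7, it says that "this is equivalent to an effect size of 0.55". The first step is at client level: "To achieve a power of 80% with an alpha of 0.05 (using two-tailed tests) requires a minimum sample size of 54 clients per group". The second is for attrition: "Considering an expected drop-out rate of 30% before post-test, a total sample size of 154 older adults is needed". The last is for clustering and unequal team sizes, "taking into account an intraclass correlation of 0.02 and a coefficient of variation of 0.50, resulting in a total sample size of 260 older adults". The number of teams does not enter this calculation.

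The Randomisation section fixes the design: "ten nursing teams in five working areas (two teams per area) will be selected", and these are "randomised into either the intervention or control group within each working area". Each area therefore supplies one team per arm. Under Data analyses, Effect evaluation, team is a random effect because it is the unit of randomisation. Working area and its interaction with time are predictors. The same paragraph notes that the team effect cannot be separated from an area-by-treatment interaction.

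**The concern.** A design effect corrects the variance of the arm difference for clustering. It does not correct for having to estimate the between-team part of that variance from a handful of teams. With many clusters the second correction is negligible. With five pairs it is not, because the t critical value on 4 df is about 40% larger than the one behind the 54 per group (2.776/1.983 = 1.40).

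What is at stake is how the result is read. A null finding would be taken to come from a trial with 80% power for a 15% difference, when the inputs given support less than that for the comparison on which the trial was sized. The Discussion already says that 12 months may be too short to show effects, so a null result is a real possibility.

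**Working it through.** **Inputs.** From Sample size: mean 535.9, SD 145.7, difference 15%, d = 0.55, two-sided alpha 0.05, 54 per group, dropout 30%, ICC 0.02, CV 0.50, N = 260. From Randomisation: ten teams, two in each of five areas. From Effect evaluation: team random, area in the model.

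**1. The plan's own figures**
- Effect size: 0.15 × 535.9 = 80.4 min/day; 80.4/145.7 = 0.552, stated as 0.55.
- Client-level step: the non-central t gives 80.1% power at 53 per group and 80.8% at 54 (106 df, critical value 1.98). The 54 is adequate.
- Dropout: 108/0.7 = 154.
- Clustering at 260/10 = 26 clients per team: 154 × [1 + (26 − 1) × 0.02] × (1 + 0.5²/2) = 154 × 1.5 × 1.125 = 259.9, which matches 260. The factor 1.125 is inferred from the figures; the article does not print it.

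**2. Team-level degrees of freedom**
- Ten teams, less one for the mean, four for the areas and one for the arm: 10 − 1 − 4 − 1 = 4. Critical value 2.776.
- If the pairing is ignored: 10 − 2 = 8. Critical value 2.306.

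**3. Power of a post-test comparison**
- Evaluable clients: 0.7 × 260 = 182, or 18.2 per team.
- Design effect (DE) allowing for unequal team sizes: 1 + [(1 + 0.25) × 18.2 − 1] × 0.02 = 1.435.
- Effective n per arm: 182/1.435/2 = 63.4.
- Non-centrality: 0.55 × √(63.4/2) = 3.10.
- Power is the probability that a non-central t with this non-centrality exceeds the critical value.

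The choice of design effect matters, so the range is shown (d = 0.55, 182 evaluable):

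| Design effect | DE | Normal | 8 df | 4 df |
|---|---|---|---|---|
| Equal team sizes, m = 18.2 | 1.344 | 89% | 80% | 67% |
| CV-adjusted, m = 18.2 | 1.435 | 87% | 77% | 64.5% |
| × 1.125 form, m = 18.2 | 1.512 | 86% | 75% | 62% |
| Equal team sizes, m = 26 | 1.500 | 86% | 76% | 63% |
| CV-adjusted, m = 26 | 1.630 | 83% | 72% | 59% |
| × 1.125 form, m = 26 (gives the 260) | 1.6875 | 82% | 71% | 58% |

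Every row is above 80% with a normal critical value, and every row is at 58–67% on 4 df. On 8 df the four rows that use the CV give 71–77%. The only 8-df row to reach 80% drops both the plan's CV and the pairing.

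**4. Simulation.** With unequal team sizes (mean 18.2, CV 0.5), power was 60% for an unweighted paired test of team means and 73% for the unpaired 8-df test. A mixed-model type of test that pools when the team variance is estimated as zero gave about 69%, with equal team sizes.

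**5. Detectable difference.** On 4 df, 80% power needs a non-centrality of 3.76. At DE 1.435, d = 3.76/√(63.4/2) = 0.668; × 145.7 = 97 min/day; 97/535.9 = 18%.

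**The case against.** The strongest objection is that the planned primary test is not a post-test comparison. The model has baseline and post-test within clients within teams, and the effect is the intervention-by-time interaction. A stable team effect cancels from a difference in change, and the baseline measurement can remove client variance. This stands. On 4 df with the same inputs, assuming a within-client correlation of 0.4–0.7 and 20–100% of the team variance being team-by-time, a change-score analysis has about 50–88% power and a baseline-adjusted one about 69–94%. Neither assumption has a value in the protocol. A reader might infer that the planned analysis is shown to have about 65% power; the document does not support that. The objection does not rescue the stated 80% either, because Sample size works from a cross-sectional difference and takes no credit for baseline.

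Second, area costs 4 df but may also absorb variance. The protocol does not say whether the ICC of 0.02 is within or across areas. If 25%, 50% or 75% of it lay between areas, the 64.5% would become about 68%, 72% or 76%. This also stands as a qualification, and these values remain below 80%.

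Third, the software might report larger degrees of freedom. A test on client-level df would not respect the unit of randomisation on which the analysis section insists, so it cannot support the figure.

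A reader might also infer that 260 is a miscalculation. It is not: it follows from the stated inputs, as shown in the working.

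**Conclusion.** The point holds as a missing few-cluster correction. On the stated inputs, a post-test comparison that respects the pairing has roughly 58–67% power for the 15% difference, and about 71–77% with the CV-adjusted design effects if the pairing is ignored. The difference detectable with 80% power on 4 df is about d = 0.67 (97 min/day, 18%) at design effect 1.435.

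These figures assume 182 evaluable clients, an ICC of 0.02 that is entirely between teams within areas, and no gain from baseline. The shortfall from 80% is firm for the comparison that the section sizes. The exact figure within the range is not, because it depends on the design-effect formula. Power for the planned intervention-by-time contrast is undetermined: it may lie above or below 80%. The finding therefore does not show that the trial is too small, only that the power stated for it is not supported by the calculation given.

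**What to change.** Keep 260 clients and ten teams, and do one of the following in the Sample size section:

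- Restate the power as about 58–67% for a 15% difference, or as 80% for about 97 min/day (18%), using 4 team-level degrees of freedom and naming the design-effect formula.
- Recompute the power for the planned repeated-measures contrast on 4 df. State the assumed baseline-to-12-month correlation, the team-by-time variance and the share of the ICC that lies between areas, and show the range over plausible values.

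Either way, print the factor used for unequal team sizes, so that the step from 154 to 260 can be followed. The cost is a less favourable stated figure, or in the second case possibly a wide range. No extra clients or teams are needed.

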### Data management

Data are handled confidentially and results will presented in an anonymised way. All original study forms will be entered electronically in Excel 2016 and kept on file at Maastricht University. Forms are stored in numerical order and in a secure and accessible place and manner for a period of 10 years after completion of the study. All records that contain names or other personal identifiers, such as informed consent forms, will be stored separately from study records identified by code number. All local databases will be secured with password-protected access systems. Forms, lists, logbooks, appointment books, and any other listings that link participant ID numbers to other identifying information will be stored in a separate, locked file in an area with limited access. Only two of the involved researchers (authors [name], [name]) will have access to the complete final dataset. Data integrity will be enforced through a variety of mechanisms (i.e. double data entry, range checks for data values). Data will be coded using digital codebooks, which are created for each questionnaire or registration form prior to the start of the study. The option to choose a value from a list of valid codes and a description of what each code means will be available where applicable.

### Data analyses

Missing item responses within a given scale will be replaced by mean imputation [65] using the mean of that client on the other items in that scale at that time point of measurement, assuming that the number of missing item responses does not exceed the missingness percentage suggested by the developers of the given scale. If this information is not available, a missingness percentage of 25% is accepted.

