#### Secondary outcome measures

The LASA Sedentary Behaviour questionnaire [46] will be used to assess self-reported sedentary behaviour. The questionnaire consists of 10 items about sedentary activities such as watching television. Older adults will report the time that they generally spent on each sedentary activity per day. The items must be completed for one weekday and one weekend day. Total self-reported sedentary time (in minutes) for an average day will be calculated as ((total sedentary time on weekdays * 5) + (total sedentary time on weekend days * 2))/7. A previous study has shown that self-reported sedentary time measured by the LASA Sedentary Behaviour questionnaire can reliably rank sedentary time in in older persons and was moderately associated with accelerometer-derived sedentary time [46].

Physical functioning will be measured by the Short Physical Performance Battery (SPPB, [47]). The SPPB is based on three objective tests of physical function: 3-m walking speed, repeated chair stands (five times), and standing balance in progressively more-challenging positions (i.e. feet in side-by-side, semi-tandem, and full-tandem positions). Each test is scored 0 to 4 by previously determined criteria [48]. Scores from the three tests will be summed into a composite score ranging from 0 to 12, with higher scores reflecting better physical functioning. The SPPB has excellent reliability [49] and is highly sensitive to important changes such as self-reported decline in ability to walk a block or to climb one flight of stairs. Decreased SPPB is a strong predictor of nursing home admission, disability in self-care tasks, and mobility in older adults [48, 49].

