#### Clinical outcomes

The primary outcome measure for the CEA will be sedentary time. The primary outcome measure for the CUA will be generic quality adjusted life years (QALYs), measured by means of the standard newest Dutch version of the EuroQol-5D-5 L. (EQ-5D-5 L, [56, 57]). The EQ-5D-5 L consists of five dimensions of health-related quality of life, namely mobility, self-care, daily activities, pain/discomfort and depression/anxiety. Each dimension can be rated at five levels: ranging from ‘no problems’ to ‘major problems’ [58, 59]. The five dimensions can be summed into a health state. Utility values can be calculated for these health states, using preferences elicited from a general population, the so-called algorithm [60]. The utilities at the three time points (baseline and 6 and 12 months after baseline) will be used to calculate QALYs by means of the area under the curve method. In addition, the EQ visual analogue scale will be used to assess current health status [58, 59].

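### One person-mean rule for missing items has no exception by instrument, so it can reach LASA minutes and EQ-5D-5L levels, which it does not suit

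*Protocol article*

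**What the plan says.** The opening paragraph of Data analyses stands ahead of the effect and economic subsections and sets one item-level rule: "Missing item responses within a given scale will be replaced by mean imputation", "using the mean of that client on the other items in that scale at that time point of measurement". Its condition is that the number of missing items "does not exceed the missingness percentage suggested by the developers of the given scale". There is a fallback: "If this information is not available, a missingness percentage of 25% is accepted". The developers' limits are not given for any instrument, and no instrument has a rule of its own.

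Two instruments matter here.
- **LASA Sedentary Behaviour questionnaire** (Secondary outcome measures): "The questionnaire consists of 10 items about sedentary activities such as watching television". Answers are times, given once for a weekday and once for a weekend day. The two day totals are weighted 5/7 and 2/7.
- **EQ-5D-5L** (Clinical outcomes, under Economic evaluation): "The EQ-5D-5 L consists of five dimensions of health-related quality of life", "namely mobility, self-care, daily activities, pain/discomfort and depression/anxiety". Each has five levels. The resulting health state is turned into a utility by a preference-based algorithm, and utilities at 0, 6 and 12 months give the QALYs.

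**The concern.** A client's mean on the answered items is a reasonable stand-in for a missing one when the items share a response format, measure much the same thing and are summed. PHQ-9 fits that description, and GARS largely does.

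LASA does not. Time spent on other activities is no estimate of time spent watching television, and the error changes sign with the item that is blank. The EQ-5D-5L does not fit either. Its dimensions are distinct, its levels are discrete, and its score is a valued profile, not an item mean. A fractional level belongs to no health state, and the paragraph gives no rounding rule.

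At stake are one self-reported secondary outcome and the QALYs of the cost-utility analysis.

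**Working it through.** The protocol gives no figure of its own on this point, so there is none to reproduce. Three checks follow.

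**1. Where the 25% fallback lets the rule act.** Items that may be filled = floor(0.25 × number of items), with item counts from the protocol.

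| Instrument | Items | Items that may be filled |
|---|---|---|
| LASA | 10 | floor(2.5) = 2 |
| EQ-5D-5L | 5 | floor(1.25) = 1 (20%) |
| GARS | 18 | floor(4.5) = 4 |
| PHQ-9 | 9 | floor(2.25) = 2 |
| SPPB | 3 | floor(0.75) = 0 (one missing is 33%) |

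**2. LASA.** With k of 10 items missing on a day, person-mean filling gives: day total = observed sum × 10/(10 − k).

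The protocol gives no item values. Assume television at 120 to 240 min, the other nine items at 40 min each, the same profile on both days, and filling within each day.
- True day total: 120 + 9 × 40 = 480, up to 240 + 9 × 40 = 600.
- Television missing: 360 × 10/9 = 400. Error: 400 − 480 = −80, to 400 − 600 = −200 min.
- Missing for both days: the weighted daily total is 80 to 200 min too low.
- Missing for the weekday only: 5/7 × 80 = 57, to 5/7 × 200 = 143 min too low.
- Missing for the weekend day only: 2/7 × 80 = 23, to 2/7 × 200 = 57 min too low.

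The error can go the other way. Let the missing item be truly 0 min on both days, with television as above and the other eight items at 40.
- Television 120: the true total is 440 and the filled total is 440 × 10/9 = 489, so 49 min too high.
- Television 240: the true total is 560 and the filled total is 560 × 10/9 = 622, so 62 min too high.
- In both cases the excess is 11%. With two true-zero items missing it is 10/8 − 1 = 25%.

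These are errors for one client. If a share p of an arm lacks the television item for both days, the arm mean falls by p × 80 to p × 200 min. With p = 5% (an assumption) that is 4 to 10 min. Equal p in both arms would largely cancel in the comparison.

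**3. EQ-5D-5L.** With one dimension missing, four levels from 1 to 5 are observed, giving 5^4 = 625 possible patterns. The imputed value is a valid level only if the four levels sum to a multiple of 4.
- This holds for 157 patterns. The other 625 − 157 = 468 (468/625 = 74.9%) give a fractional value.
- Example: levels 3, 3, 2, 1 give 9/4 = 2.25.

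The count weights all patterns equally; real profiles are not equally common.

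By the trapezoid rule, the 12-month QALY is 0.25 × U0 + 0.5 × U6 + 0.25 × U12, so the 6-month utility carries half the weight.

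**The case against.** - **The developers' limit comes first.** A reader might infer that the rule acts on every scale. The text does not support that. Where developers allow no missing item, the rule never acts on that instrument, and the protocol does not say what the LASA or EQ-5D-5L developers allow. Under the fallback, SPPB is never filled. This stands, and the point is worded accordingly. But the clause limits only how many items may be filled, not how.
- **Wrong or corrupted utilities are not shown.** A fractional level yields no utility at all until a further step is added, and a condensed article may leave scoring steps to another document. That stands against calling the utilities corrupted. The filling method is nevertheless stated, and in most patterns it cannot be carried through to a utility as written. The 157 whole-number patterns do yield a valid level, though still one borrowed from other dimensions.
- **The LASA error should not be set against the trial's target difference.** The target is 15% of 535.9 min, about 80 min. It is a difference between group means on the accelerometer. The LASA figures are errors in one client's total on another instrument. The comparison does not hold.
- **Item non-response may be rare.** Effect evaluation says research staff working to a protocol collect all the data, with monitoring. That is plausible and limits the likely size, but no rate is given.
- **The care-use questionnaire.** A reader might extend the rule to its nine items. The protocol calls it a questionnaire on volumes of care and gives it no scale score, so this reading is not supported.

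**Conclusion.** The point holds as a defect in a stated rule, with limited reach. Unless a developer limit excludes them, up to 2 of 10 LASA items and 1 of 5 EQ-5D-5L dimensions would be filled by a method that does not suit them. For LASA the error for a client can be small or large and of either sign; the 80-200, 57-143 and 23-57 min figures rest on the assumed item profile. For the EQ-5D-5L, 75% of patterns (unweighted) leave no defined health state.

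The primary outcome comes from the accelerometer and has no items to fill. The effect measure of the cost-effectiveness analysis is the same accelerometer measure. A reader might infer a biased treatment effect on self-reported sedentary time or on QALYs. The document does not support that step: it depends on an item-missingness rate, and on a difference in that rate between arms, and neither is given.

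**What to change.** Reword the opening paragraph of Data analyses in three respects.
1. Limit person-mean imputation to summed scales with a common item format, naming GARS and PHQ-9, and keep the developer limit and the 25% fallback for those.
2. Set a LASA total with any missing item to missing. The mixed model already planned under Effect evaluation uses all available data, so LASA needs no multiple imputation. This relies on the totals being missing at random.
3. Set an incomplete EQ-5D-5L utility to missing and impute it at utility level, for example by multiple imputation using arm and the utilities at the other time points.

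The cost is a few sentences, a little more programming and a few more missing LASA totals. No new data are needed.
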